## Abstract

Recently, a large cluster-randomized controlled trial was designed—Music Interventions for Dementia and Depression in ELderly care (MIDDEL)—to assess the effectiveness of music interventions on depression in care home residents with dementia (ClinicalTrials.gov NCT03496675). To understand the pathophysiological mechanisms, we observed the effect of repeated music interventions on stress in this population since chronic stress was associated with depression and an increased risk for dementia. An exploratory study was designed to assess: (1) changes in hair cortisol concentrations as an indicator of longer-term stress; (2) whether baseline stress is a predictor of therapy outcome; (3) pre- and post-treatment effects on salivary α-amylase and cortisol response as an indicator of immediate stress in 180–200 care home residents with dementia and depressive symptoms who partake in the MIDDEL trial. Insights into mediatory effects of stress to explain the effect of music interventions will be gained. Hair cortisol concentrations were assessed at baseline and at 3, 6, and 12 months along with the Perceived Stress Scale. Salivary α-amylase and cortisol concentrations were assessed at 1, 3, and 6 months. Saliva was collected just before a session and 15 and 60 min after a session, along with a stress Visual Analogue Scale.

## 1. Introduction

Recently, a large cluster-randomized controlled trial was designed—Music Interventions for Dementia and Depression in ELderly care (MIDDEL)—from which the effectiveness of music interventions on depression in care home residents with dementia is assessed (ClinicalTrials.gov registration NCT03496675) [1]. Care home units (CHUs) and their residents are randomly allocated to one of four arms: group music therapy (GMT), recreational choir singing (RCS), the combination of both music interventions, or the control group receiving care as usual. Each intervention is offered twice a week for three months and once a week during the following three months. The primary outcome is depressive symptoms at 6 months, measured with the Montgomery–Åsberg Depression Rating Scale (MADRS) [2]. The RCT design, large sample size, and international collaborations within the MIDDEL trial (trial registration number NCT03496675) offer an excellent opportunity to implement this exploratory biomarker add-on study.

Besides investigating the effect of music on depressive symptoms, it is relevant to look at the effect of repeated music interventions on stress in care home residents with depressive symptoms, especially since chronic stress has been associated with depression and an increased risk for dementia. In the context of disease, stress—which is usually adaptive—can have negative effects on health and quality of life when prolonged [3,4]. Due to the body’s incapacity to cope with ongoing stress and the related physiological processes, so-called allostatic load occurs, which ultimately leads to illness [5]. In this sense, dementia is not caused by stress, but its manifestation might be facilitated by ongoing stress—and development might be accelerated (e.g., in care home residents) [6,7,8]. A recent review highlights the intricate association between depression and dementia and the accelerating and worsening effect that depression can have on the development of dementia. The authors attribute long-term dysregulations in the immune system, which can arise from chronic stress, as a possible underlying factor associated with both depression and dementia developments [9]. Similarly, Linnemann et al. (2020) described that stress, expressed in elevated cortisol levels and increased hypothalamus–pituitary–adrenal (HPA) axis activity, is one of the possible pathways connecting depression and dementia. Elevated cortisol levels were observed in 70% of depressed patients and also in people with Alzheimer’s, as shown in the review [10]. Chronic stress can elicit depression, yet, it is still unclear which neural pathways contribute to chronic stress leading to depression [11,12,13]. In a meta-analysis by de Witte et al. (2019) [14], music interventions were found to have a significant effect on the reduction in both physiological and psychological stress.

The response of the different components of stress-response systems can be measured using various biomarkers, such as cortisol and α-amylase [15]. Cortisol is a marker of the HPA axis [6,16]. Cortisol and α-amylase levels show an opposite rhythm throughout the day. Cortisol decreases during the day and increases at night; for α-amylase, vice versa [17]. Cortisol shows a peak approximately half an hour after awakening, whereas α-amylase typically declines at that time [17]. Cortisol concentrations then decrease throughout the day, whereas α-amylase increases and shows a peak late in the afternoon or in the evening [18]. Cortisol levels may fluctuate due to pulsatile secretion, the diurnal rhythm, and acute stress [19].

α-amylase is a marker for the autonomic nervous system (ANS) that can reflect stress-related changes [16,20]. The HPA axis and cortisol as markers of stress are well known and widely used. However, the importance and role of the ANS axis are becoming increasingly prevalent, with the salivary enzyme α-amylase being one of its reliable markers [5]. The activity of α-amylase increases in response to stress and can reflect the activity of the ANS and psychological and behavioral stress [4,5]. Indeed, previous studies found that psychological stress may affect sAA secretion, as it reflects ANS activity [21,22,23]. sAA was examined in behavioral medicine in different samples to identify patterns of dysregulations of the ANS (e.g., due to being exposed to chronic stress), gain insight into the application of sAA assessment to differentiate between treatment and control groups, and assess the effectiveness of various (stress-reducing) interventions [5]. Cortisol is commonly elevated in the elderly [8]. Elevated cortisol levels have been associated with poorer cognitive abilities, a higher risk of cognitive decline, and faster cognitive decline [7]. Several hair cortisol (HC) studies showed that chronic stress has a detrimental impact on daily functioning, engagement in social activities, and wellbeing/quality of life [24]. However, in a feasibility study, HC levels did not seem to be affected by medical conditions, cognitive dysfunction, psychotropic drug use, or behavioral problems [25] (p81). Cortisol levels may also be higher in people with depression [19,26]. To illustrate, Booij et al. [15] found higher SC and salivary α-amylase (SAA) levels, a steeper daily cortisol slope and a larger SAA over SC ratio in depressed than in non-depressed adult participants.

Cortisol and SAA were assessed in multiple psychotherapeutic intervention studies [6]. Non-pharmacological interventions in people with dementia may have a lowering effect on cortisol levels [7]. The two most commonly investigated pathways of these stress hormones are the use of pre-intervention cortisol concentrations as a treatment response predictor and the use of cortisol and α-amylase as an outcome measure to assess changes over time during the intervention period [6]. Interventions that aim to decrease HPA axis dysregulation may strengthen protective factors for the elderly. For example, such interventions may improve emotional regulation, offer social support, and reinforce resilience [8].

Biomarkers are increasingly used to investigate the potential stress-reducing effect of listening to music and music-making [16,26,27,28,29]. However, so far, relatively little research has been conducted to assess the effect of music-making on biomarkers, such as cortisol levels, in people with dementia and/or depressive symptoms.

The primary objective of this study was to assess the effect of repeated music interventions on chronic stress in care home residents with dementia and depressive symptoms. The differential effect of RCS, GMT, and RCS plus GMT was compared to care as usual. Secondary objectives were to assess whether the baseline level of chronic stress, as indicated by HC, is a predictor of therapy outcome (reduction in depressive symptoms) and to assess the immediate effect of music interventions on stress. As high depression scores correlate with higher HC concentrations, we hypothesized that participating in a music intervention would result in lower HC concentrations, with greater changes in the intervention groups than in the control group. The design of this study meets requirements to tackle frequent limitations in studies of HPA axis and/or ANS activity in music interventions in people with dementia, given the intervention duration, repeated assessments, control group for comparison, assessing both immediate and longer-term intervention effects [30].

## 2. Materials and Methods

### 2.1. Design

This study is a part of the large, multinational cluster-randomized controlled trial Music Interventions for Dementia and Depression in ELderly care (MIDDEL) (ClinicalTrials.gov registration NCT03496675) [1]. In the present exploratory substudy, participants from all four arms (GMT, RCS, GMT plus RCS, or control group) of the original trial from Norway, Germany, and the Netherlands were included (Figure 1). For the part of the substudy addressing immediate effects using saliva samples, only three arms (GMT, RCS, control group) were included. This limits participant burden and prevents uncertainty about which music intervention may have caused a certain effect in the combination group receiving both GMT and RCS. The primary outcome of the main trial was depressive symptoms at 6 months, measured with the MADRS [2]. For additional information about the main trial, study design, and procedures, see Gold et al., 2019 [1].

Chronic stress can be assessed objectively from cortisol in hair samples, as hair cortisol (HC) provides insight into cortisol levels over a longer period of time [4,25]. Sampling HC is an objective, easy, non-invasive, and affordable way of assessing chronic stress in people with dementia [19,24,25]. HC represents the longer-term retrospective activity of the HPA axis, which, in turn, is associated with chronic stress [31].

Measuring cortisol and α-amylase in the saliva is a non-invasive, easy, and reliable way to assess stress on health outcomes [3,4,5]. Assessment of stress in SC concerns real-time data, and especially in times of stress, there are significant correlations between cortisol concentrations in saliva and blood [4]. The digestive enzyme α-amylase can be measured from the same saliva sample to assess stress [5]. To date, SAA has only been assessed in a few clinical samples [5]. Hence, by examining both biomarkers—which can conveniently be analyzed with the same sample—a more complete picture of immediate physiological stress can be obtained [32].

### 2.2. Participants

Approximately 180–200 care home residents from 20 CHUs participating in the MIDDEL trial were included in this substudy (Figure 1). Care home residents were included if they were aged 65 years or older; resident (full-time, 24 h/day) at a participating CHU; had dementia as indicated by a Clinical Dementia Rating (CDR) score of 0.5 to 3 and a Mini-Mental State Examination (MMSE) score of 26 or less; had at least mild depressive symptoms, as indicated by the MADRS score of at least 8; had a clinical diagnosis of dementia according to the International Classification of Diseases and Related Health Problems 10 (ICD-10) research criteria; and provided written informed consent (IC) (optionally by proxy). Care home residents in different dementia stages were included. In line with the main MIDDEL trial protocol [1], where possible, the MADRS assessment was based on an interview with the participant. All relevant clues and information from other sources were used as a basis for the rating if the assessor was unable to obtain definite answers. Most participants were unable to report on themselves; hence, proxy informants were asked to report perceived stress on the Visual Analogue Scale.

The exclusion criteria were those diagnosed with Parkinson’s disease or schizophrenia, severe hearing impairment, being in short-term care, and not being able to sit down during (at least part of) the session. For saliva sample collection, additional exclusion criteria were having swallowing difficulties and being in the intervention group receiving both GMT and RCS. For hair sample collection, the additional exclusion criteria were those who did not have sufficient hair. In order to eliminate the risk of ingestion, residents with swallowing difficulties, indicated by physician and nurse reports, were excluded. Saliva samples were not collected in residents judged by care staff to be unable to follow the procedure, which may commonly be the case in residents with severe dementia (CDR = 3).

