### 2.3. Randomization

Participants that were part of the MIDDEL trial were therefore randomized with their CHU to one of four groups: GMT, RCS, GMT plus RCS, or the control group. Randomization took place at the central study office after the completion of baseline assessments, using a computer-generated randomization list with a block size of four.

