### 2.5. Control Condition

The book reading served as a control condition for residents in the standard care group at T1 (within 1 month after completion of baseline assessment) and at T3 (3 months) and T6 (6 months). The control condition was similar to the music sessions in terms of group size, duration, and time of assessment. Hence, every book reading session took place around 15:00 h in the afternoon. All participating residents from the CHU participated in the book reading session. This session lasted 45 min. The book reading session was organized and supervised by either a volunteer, research assistant, research nurse, or care staff. This can also be the responsibility of one of the persons collecting samples before and after the session. The book reading session has an interactive character and functions as a social activity. A range of reading activities can be selected, such as reading local news stories, short stories, talking about headlines, and flipping through a magazine with pictures. Residents may read themselves or with the guidance of the supervisor if necessary. To illustrate, residents can read the paper and talk about headlines, whereas residents unable to read can flip through a magazine with pictures.

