#### 2.6.3. Secondary Study Parameters: Salivary Cortisol and Alpha-Amylase

SC can provide more insight into how well the endocrine stress system responds to an immediate intervention because HC does not provide insight into how well the HPA axis functions. As residents with depressive symptoms were expected to have steeper cortisol slopes, we hypothesized that participants have a higher SC before the start of the music session, and participating in the music intervention attenuates the SC. Samples were collected on days a music or book reading session took place, between 12.00 and 17.00 h, preferably at 15.00 h, to minimize any confounding effects of the diurnal hormonal rhythm. In order to assess the immediate effects of music interventions on stress, saliva samples were collected to assess SC and SAA levels just before, 15 min after, and 60 min after the music/book reading session. Multiple measurements of SC and SAA per resident were required because of variations in levels over time within residents [15]. The assessment took place at T1 (within 1 month after the music interventions started or within 1 month after completion of the baseline assessment in the control group), T3 (3 months), and T6 (6 months). The days were selected according to logistic convenience (the first session that took around 15.00 h around T1, T3, and T6 were selected).

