#### 2.7.2. Saliva Sample Collection

Residents were asked to collect the saliva using longer-length Salivettes (Salivettes, Sarstedt, Sevelen, Switzerland) and small cotton rolls originally devised for infants and young children, and the swab could be held by the research nurse, who was assisting with the sample collection. Although the use of Salivettes is not optimal to assess SAA, after careful consideration, we choose the use of longer-length Salivettes (SalivaBio Children’s Swab method) over the use of a passive drooling technique, as this was expected to be safe (eliminate the risk of ingestion), feasible, easy to learn and perform, and clean [20]. Hereby, we also took into account our expectation that a proportion of participating care home residents with dementia and depressive symptoms have difficulty understanding instructions and experience dry mouth due to age and medication use. Care staff received instructions prior to the day of sample collection, asking them to help residents—where possible—avoid physical exercise and chewing gum (24 h); consuming caffeinated and alcoholic beverages, juice, and tobacco (18 h); psychotropic drugs (6 h); brushing teeth; and eating or drinking (1 h) before the collection of the saliva sample. A short questionnaire was filled out by the proxy (care staff) to assess adherence to instructions prior to sample collection. Prior to the first collection of saliva samples (T1), residents practiced the saliva collection procedure when necessary to become familiar with the process.

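### Saliva sampling depends on a care-staff judgement that has no stated criterion and need not precede randomisation, so selection that differs by arm cannot be excluded.

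*Protocol article*

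**What the plan says.** All references are to the protocol article.

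- **Who is sampled (section 2.2).** "Saliva samples were not collected in residents judged by care staff to be unable to follow the procedure". Severe dementia is mentioned as a common instance of such inability, not as the rule. The other saliva exclusions are listed as follows: "additional exclusion criteria were having swallowing difficulties and being in the intervention group receiving both GMT and RCS". Swallowing difficulty is taken from physician and nurse reports.
- **When units are allocated (section 2.3).** "Randomization took place at the central study office after the completion of baseline assessments". Residents are randomised with their unit.
- **When saliva is taken (section 2.6.3).** The first occasion is "T1 (within 1 month after the music interventions started or within 1 month after completion of the baseline assessment in the control group"). T3 and T6 follow. There is no saliva sample at T0.
- **Practice (section 2.7.2).** "Prior to the first collection of saliva samples (T1), residents practiced the saliva collection procedure when necessary".
- **What is compared.** In section 2.1, for saliva, "only three arms (GMT, RCS, control group) were included". Section 2.10.2 plans a description of the amylase and cortisol responses and says that the design accounts for differential responses in three groups.
- **Care staff and the arms (section 2.5).** The control book reading is "organized and supervised by either a volunteer, research assistant, research nurse, or care staff". The article says nothing about whether care staff are blinded, and it does not date their judgement of ability.

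**The concern.** The immediate effect of music on stress is a stated secondary objective (section 1), and the book-reading session was set up as the comparator for it. Randomisation makes the three saliva groups comparable only if residents enter them by the same process in each arm. Here entry depends on a subjective judgement by people who work on the unit, and nothing requires that judgement before allocation. If staff in music units, having seen residents take part in sessions, judge ability more generously than staff in control units (or the reverse), the sampled groups would differ in impairment for reasons unrelated to any effect of music. Residents judged unable contribute no saliva data at all, so the analysis could not recover them.

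**Working it through.** **1. The plan's own figure.** The only effect size in the article is d = 0.51 (section 2.9). Inputs: 160 participants, so 80 per side of each factorial margin; ICC 0.01; cluster size 8; two-sided 2.5%; 80% power. The design effect is 1 + (8 − 1) × 0.01 = 1.07, and the effective number per side is 80 / 1.07 = 74.8. A two-sample t-test then detects d = 0.509, so the figure reproduces. It concerns the long-term outcomes and does not bear on who gives saliva. No stated figure does.

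**2. Order of events.** Baseline assessments, then randomisation of the unit, then music twice a week (section 2.4), then saliva at T1 within one month. By T1 a resident of a GMT or RCS unit may have been offered up to about 2 × 4 = 8 sessions. Practice is placed before T1 but not before randomisation. The ability judgement has no date.

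**3. Do staff know the arm?** The article does not say. Whole units are allocated, RCS may involve all residents of a unit, and care staff may run the control session. Knowledge of the arm is very probable, but it is an inference.

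**4. When would this bias the contrast?** Suppose staff keep the most able share q of residents, and ability has correlation ρ with the outcome in the absence of any music effect. The mean ability of those kept, in SD units, is m(q) = φ(z) / q, where z is the standard normal quantile at 1 − q. The bias between two arms is ρ × [m(q1) − m(q0)]. All shares and correlations below are assumptions.

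| Shares sampled | m values | Difference | Bias for ρ = 0.1 to 0.5 |
|---|---|---|---|
| 80% / 80% | 0.350, 0.350 | 0 | 0 |
| 80% / 70% | 0.350, 0.497 | 0.147 | 0.015 to 0.07 SD |
| 80% / 60% | 0.350, 0.644 | 0.294 | 0.03 to 0.15 SD |
| 90% / 60% | 0.195, 0.644 | 0.449 | 0.05 to 0.22 SD |

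The first row is the important one: the same selection in every arm gives no bias. Equal shares do not prove equal selection, however. With 80% sampled in both arms but ρ = 0.1 in one and 0.3 in the other, the bias is (0.3 − 0.1) × 0.350 = 0.07 SD. Shares alone are therefore not a sufficient check.

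**5. Level or response?** For the pre-session level, ρ is the correlation of ability with level. For the change from before to after the session, ρ is the correlation of ability with the change. A shift that is constant within a resident gives ρ = 0 for the change and drops out. Bias in the response needs ability to be related to the size of the response itself, and the documents give nothing on that.

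**6. Scale.** With 40 residents per saliva arm after 20% dropout, in five units of eight (20 units over four arms), a pairwise comparison at two-sided 5% detects about d = 0.66. With 70% of residents sampled it detects about 0.78. The assumed biases are small beside these.

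**The case against.** **Nothing in the article says that staff judge after allocation or unblinded.** Correct. A reader might infer that unblinded staff decide eligibility once the arm is known. The text neither states this nor rules out a judgement at baseline.

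**The exclusion of the combination arm shows nothing about timing.** Also correct. Because the allocated arm appears among the saliva exclusions, one might conclude that all saliva eligibility is settled after allocation. Section 2.1 shows that this exclusion removes a whole arm by design, to limit burden and avoid doubt about which intervention acted. It does not say when an individual's ability is judged.

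**The mechanism is speculative.** The task is to hold or gently chew a cotton roll for a minute or two, with a research nurse able to hold the swab. Residents live on the unit full-time, so staff in every arm see daily how they eat, drink and follow instructions. This makes a large difference between arms less likely. It does not exclude one, because the judgement has no criterion.

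**Imbalance could be detected without baseline saliva.** This stands. CDR, MMSE and MADRS are inclusion measures, and hair cortisol and PSS-10 are collected at T0. Sampled and unsampled residents can be compared on them by arm.

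**A condensed article leaves operational timing to fuller documents.** A missing date alone would be no finding. But the article does fix who judges, ties sampling and practice to T1, and places randomisation before that. Moving the judgement ahead of allocation improves the design beyond supplying an omitted detail.

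**Conclusion.** The point holds as a risk of selection that differs by arm, confined to the secondary saliva comparison of GMT, RCS and control. It rests on three textual facts: a subjective judgement without a criterion, no requirement that it precede randomisation, and sampling and practice tied to T1. It also rests on one strong inference, that staff on a unit know its arm.

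It is not an established bias. No magnitude can be derived from the documents; the 0.015 to 0.22 SD above comes wholly from assumed shares and correlations, and much of any level shift would cancel in the within-resident response. Selection that works alike in all arms limits generalisability only. The co-primary outcomes, hair cortisol and PSS-10, do not pass through this judgement and are unaffected. The change is worth making because it is cheap and removes a recognised selection risk in cluster trials.

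**What to change.** At T0, before the unit is randomised, have care staff record two items for every substudy resident: swallowing status, and ability to follow the saliva procedure against a criterion written in the protocol. Practice remains only where necessary. Define the saliva cohort from that record. After allocation, remove only the GMT + RCS units, as whole units. Count a cohort member who later cannot give a sample as missing, not as ineligible. This changes when eligibility is recorded, not the swallowing exclusion itself.

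Report, by arm, the share of the cohort sampled and the reasons for not sampling. Compare sampled with unsampled residents by arm on T0 CDR, MMSE, MADRS, hair cortisol and PSS-10.

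The cost is a short checklist entry per resident, which goes unused in units later allocated to GMT + RCS. It does not by itself recover data from residents who cannot be sampled; it makes their number and type visible by arm. If randomisation has already taken place in some units, the reporting and the T0 comparison can still be done there.
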